### Primary outcome measure

#### Angina symptoms

The primary outcome measure is the change in angina symptoms from baseline to 12 months, which will be compared between the intervention and control group to answer the main research question. The quantity of angina symptoms will be evaluated by the shortened Seattle Angina Questionnaire (SAQ-7) [29]. The SAQ-7 has good validity and reproducibility in patients with angina pectoris and correlates with prognosis [29]. Furthermore, through its limited length it can easily be used in routine clinical practice.

### Secondary outcome measures

#### Clinical outcomes

Secondary clinical outcome measures include ischemic threshold, major adverse cardiac events, health-related quality of life, physical fitness, cardiovascular health, psychosocial wellbeing and physical activity pattern. See Table 3  for the assessment schedule.Ischemic threshold is evaluated at baseline and 1 year and is defined as the exercise intensity (Watts) at which ECG abnormalities occur during symptom-limited exercise testing. If no ischemia is observed at follow-up, the maximal achieved workload in watts will be used. Ischemia is defined as at least 1.5 mm ST-segment depression in ≥ 2 leads or ≥ 2 mm ST-segment depression in a single lead at < 7 metabolic equivalents. This measure is frequently used to examine the impact of (non)pharmacological strategies in SAP patients and is strongly linked to clinical outcomes [30]. The ischemic threshold of every exercise test will be assessed by two cardiologists from the study team who are blinded for randomisation. All patients perform a supervised symptom-limited exercise test on a cycle ergometer, using an individualised ramp protocol with duration of 8 to 12 min. Although being individualised, the protocol will be kept similar within individuals. The test is ended when a patient is not able to maintain the required pedalling frequency of 70 per minute. A 12-lead electrocardiogram is registered continuously.Major adverse cardiovascular events are evaluated using the International Classification of Disease-10. We will record occurrence of death of cardiac cause, non-fatal myocardial infarctions, (repeated) myocardial revascularisations (specified to urgent and non-urgent) and unplanned hospitalisation owing to worsening angina. Revascularisation is considered to be urgent when a patient is admitted to the hospital with persistent or increasing chest pain (with or without ST-segment or T-wave changes or elevated biomarker levels) and the revascularisation procedure was performed during the same hospitalisation. These data are extracted from the electronic patient record at 1-year follow-up. This will be double checked with the patient during the last (12-month) study visit.Health related quality of life is evaluated at baseline, 3, 6, 9 and 12 months, using the EQ-5D-5L questionnaire in a validated Dutch version [31].All participants perform a supervised symptom-limited exercise test at baseline and 12 months. To examine physical fitness, we also record peak workload, expressed in watts which represents a surrogate for physical fitness level.To examine cardiovascular health, general cardiovascular risk factors are assessed at baseline, 3 and 12 months. This includes blood pressure, lipid profile, haemoglobin A1c, fasting glucose and body-surface measurement (weight, length and body-mass index).Blood pressure measurements is performed 3 times, with a 5 min interval, at the arm with the highest value, by a heart-function technician or a member of the research team. The mean systolic and diastolic pressure is calculated.Lipid profile is evaluated by blood tests of total cholesterol, low-density lipoprotein, high-density lipoprotein, triglycerides and lipoprotein-ratio. Blood tests are performed at the patient’s own hospital and extracted from the electronic patient file.Haemoglobin A1c and fasting glucose are measured by blood tests. HbA1c levels are strongly associated with major adverse cardiovascular events and severity of coronary artery disease in patients with and without diabetes [32, 33].Body-surface measurement is performed through measurement of weight (kilogram) and length (meters) and expressed in kg/m2.To evaluate psychosocial wellbeing, both anxiety and depression are assessed at baseline, 3 months and 1 year using the HADS-questionnaire consisting of a depression subscale (HADS-D) and an anxiety subscale (HADS-A). This questionnaire is advised by latest guidelines which also provide cut-off values for the screening on anxiety and depression [18].To gain insight into lifestyle changes of both groups, sedentary behaviour and physical activity are assessed at baseline and 12 months, using the validated Sedentary behavior questionnaire (SBQ) [34] and Short questionnaire to assess health-enhancing physical activity (SQUASH) [35]

**Table 3 Tab3:**
[figure not shown]
Schedule
of enrolment, interventions and assessments

*BMI* Body mass index, *Coronary CT* Coronary
computer tomography, *EQ-5D-5L* EuroQol 5-level EQ-5D, *HADS*
Hospital Anxiety and Depression Scale, *HbA1c* Haemoglobin A1c, *hrQoL*
Health related quality of life, *iMCQ* imta Medical Cost Questionnaire, *IPCQ*
imta Productivity Cost Questionnaire, *OMT* Optimal medical therapy, *SAQ-7*
Seattle angina questionnaire-7, *SBQ* Sedentary behaviour questionnaire, *SQUASH*
Short questionnaire to assess health-enhancing physical activity

#### Cost analysis

For the second aim of this study, a cost analysis, cost-utility analysis and budget impact analysis will be performed at baseline, 3, 6, 9 and 12 months, comparing the intervention- and control group.(8)To perform the cost analysis, we will first examine the direct and indirect medical and (for the societal scenario) non-medical costs. The direct and indirect medical costs include all costs of inpatient and outpatient hospital visits, diagnostic and therapeutic procedures and consultations. The data will be collected digitally from hospital information systems and with clinical report forms. The costs of out-of-hospital care by general practitioners as well as the direct non-medical out-of-pocket expenses (over-the-counter medication) will be based on volume data gathered with repeat patient questionnaires at baseline, three, six, nine, and twelve months post randomisation. This questionnaire will be adapted to the patient group and is a shorter version of the iMCQ [36]. Unit costing will preferably be based on the existing national guideline for costing in health care research [36]. Otherwise, the unit costs especially those for hospital admissions will be assessed using hospital based absorption costing. Unit costs derived from different calendar years will be indexed to 2019 prices. Indirect cost, e.g. productivity cost, will be based on the friction cost approach, according to guideline. For the indirect cost, a shorter version of the iPCQ questionnaire will be used [36].(9)To perform the cost-utility analysis, insight into health-related quality of life is needed, which is recorded by a generic quality of life questionnaire. For a health related quality of life generic measure, we use the EQ-5D-5L questionnaire in a validated Dutch version [31].The questionnaire is held at baseline, 3, 6, 9 and 12 months of follow-up to generate health status scoring profiles over time, which will be transposed into health utilities using population based tariffs of time trade-off ratings of health states.(10)The budget impact analysis makes use of the cost information of the cost effectiveness analysis. The primary aim of this budget impact analysis is to assess the financial consequences and affordability of nationwide implementation of the comprehensive CR intervention in patients with SAP from the budget holder’s perspective (Budgettair Kader Zorg). A medium term evaluation (up to three years) will be performed based on extrapolation of the empirical findings (Cost analysis) possibly combined with secondary evidence. We will use the framework as presented in the Dutch guideline for economic evaluations [36] and we globally adhere to the ISPOR (International Society for Pharmacoeconomics and Outcomes Research) guidelines [37]. The short- and mid-term affordability of the multi-facet strategy will be assessed from different scenarios: governmental, health care (Budgettair Kader Zorg) and insurer perspectives.

### Sample size calculation

The sample size was calculated based on data from the ISCHEMIA trial, in which similar in- and exclusion criteria for SAP patients were applied as in our study [38]. The primary analysis will be based on the comparison between the two treatment arms at 12-month follow-up of the mean SAQ Summary score. The sample size assessment is based on comparing groups based on the 95% two-sided confidence interval for independent means, adjusted for baseline values (ANCOVA). The adjustment for baseline will provide an efficiency gain of 16% compared to an independent t-test, assuming a correlation of 0.4 (data from ISCHEMIA trial). The standard deviation for the SAQ summary score at 12-months is assumed to be 19 points (also data from ISCHEMIA trial). With a correction of 10% drop-out, 7% sample size gain will remain. Aiming for a power of 80% and under these assumptions, assuming equal means for both groups and a non-inferiority margin of 7 points, the required sample size is 195 patients. Accounting for 10% dropout, a total of 216 patients needs to be included.

### Statistical analyses

To test non-inferiority in reducing anginal complaints, the primary analysis will be based on the comparison of mean SAQ-score at one year follow-up between both study arms, with an intention-to-treat ANCOVA analyses. The ANCOVA analysis will be adjusted for baseline SAQ-score values and sex. In case of cross-over, meaning that a SAP patient in the intervention group requires revascularisation, the last available SAQ Summary score before the switch will be used. This is expected to be a conservative measure for demonstrating non-inferiority. Non-inferiority is proven if the upper limit of the 95% two-sided confidence interval of the mean difference between the two groups does not exceed the non-inferiority margin of 7.

Secondary endpoints will also be analysed using an intention-to-treat analysis. Differences between the two groups will assessed using ANCOVA for continuous variables and logistic regression for dichotomous variables.

Categorical baseline variables will be presented as frequencies and percentages, continuous variables as means and standard deviations, or means and interquartile ranges for variables with skewed distributions. Percentages will be calculated on the number of non-missing observations. In all cases the number of missing values will be specified.

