## Methods/design

### Design

This study is designed as a multicentre randomised controlled non-inferiority trial. Patients will be included at the cardiology department of eleven participating Dutch hospitals (Additional file 1). Patients are randomly allocated to a 12-month cardiac rehabilitation programme (intervention group) or usual care (control group). A total of 216 patients will be included, each group will consist of 108 patients (Fig. 1). All subjects are requested to provide written informed consent before study entry. Data are collected at baseline and after three, six, nine, and twelve months. The study has been approved by an ethical committee (METC Oost-Nederland, registration number 2021–12,942) and has been registered in the Netherlands Trials Register (NL9537). SPIRIT reporting guidelines were used for writing the study protocol [12].

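### The crossover rule in the primary analysis is not intention-to-treat, and its conservative direction is not assured; the stated 80% power holds only if the rule has no net effect on the rehabilitation mean

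*Protocol article*

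**What the plan says.** All references are to the protocol article.

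- **Design:** "This study is designed as a multicentre randomised controlled non-inferiority trial". On timing it says: "Data are collected at baseline and after three, six, nine, and twelve months".
- **Statistical analyses:** the primary comparison is an intention-to-treat ANCOVA of the one-year SAQ score, adjusted for baseline score and sex. Crossover is defined only for CR patients who need revascularisation. For them, "the last available SAQ Summary score before the switch will be used. This is expected to be a conservative measure for demonstrating non-inferiority". The decision rule is: "Non-inferiority is proven if the upper limit of the 95% two-sided confidence interval of the mean difference between the two groups does not exceed" the margin of 7.
- **Sample size calculation:** "The standard deviation for the SAQ summary score at 12-months is assumed to be 19 points"; "assuming equal means for both groups and a non-inferiority margin of 7 points, the required sample size is 195 patients". Dropout of 10% is allowed for, which gives 216. There is no term for crossover or for the effect of the rule on the CR mean.
- **Secondary outcome measures, Clinical outcomes:** urgent revascularisation, during an admission for ongoing or worsening chest pain, is foreseen and recorded.

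**The concern.** The label and the rule do not match. Intention-to-treat keeps each patient's outcome at the planned time whatever treatment followed. The rule discards the 12-month outcome of some CR patients because of something that happened after randomisation. That may be a legitimate target of estimation, but it is a different one and should be named as such.

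The safety claim is an expectation without support for one foreseeable pattern. Suppose a CR patient scores well at a scheduled visit, worsens, and is revascularised before the next assessment. The last available score then predates the failure, and CR is credited with it at 12 months.

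The rule acts directly on the primary contrast. A carried score that is too high makes a false claim of non-inferiority more likely. A carried score that is lower than the patient's actual 12-month score protects against that, but moves the CR mean away from the equality on which the trial was sized.

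**Working it through.** **Inputs from the article:** SD 19; baseline correlation 0.4; margin 7; true difference 0; two-sided 95% interval (one-sided 0.025); power 80%; 1:1 allocation; dropout 10%.

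**Assumed, because the article does not give them:** the crossover proportion p in the CR arm, and the mean change d, in points, that the rule makes to a crossover patient's score. Higher scores are taken as better. The shift in the CR mean is s = p × d.

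**1. The plan's own figure.** ANCOVA SD = 19 × √(1 − 0.4²) = 17.41. Total N = 4 × [17.41 × (1.960 + 0.842) / 7]² = 194.3, so 195 as stated. Dropout: 194.3 / 0.9 = 215.9, so 216 (195 / 0.9 = 216.7, a rounding difference). An unadjusted comparison needs 231.3, and 1 − 216 / 231.3 = 6.6%, the stated 7% gain. The arithmetic is right.

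**2. Precision.** With 195 evaluable (97.5 per arm), SE = 17.41 × √(2 / 97.5) = 2.494. Power with no shift = Φ(7 / 2.494 − 1.960) = 80.1%.

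**3. The effect of a shift.** If the rule raises the CR mean by s while the true deficit equals the margin, type I error = 1 − Φ(1.960 − s / 2.494). If actual means are equal and the rule lowers the CR mean by s, power = Φ((7 − s) / 2.494 − 1.960).

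| Example p × d | s | Type I error if the mean is raised | Power if the mean is lowered |
|---|---|---|---|
| no crossover | 0 | 2.5% | 80% |
| 5% × 10 points | 0.5 | 3.9% | 74% |
| 10% × 10 points | 1.0 | 6.0% | 67% |
| 20% × 10 points | 2.0 | 12.3% | 52% |

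The two right-hand columns are alternatives that arise under opposite score patterns; they do not add up. A simulated ANCOVA (20,000 runs, 97 per arm) agrees: at s = 1 and s = 2, power is 65% and 51%, and type I error is 5.7% and 12.1%.

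**4. Slack.** With no dropout at all (108 per arm), SE = 17.41 × √(2 / 108) = 2.370 and power is 84%. The downward shift that this absorbs is 7 − 2.802 × 2.370 = 0.36 points.

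**5. Size needed to keep 80%.** With 7 − s in place of 7 in step 1, equal arms and 10% dropout, the total is about 252 at s = 0.5, 296 at s = 1 and 425 at s = 2.

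**6. What s is measured against.** Against the patient's state when CR was judged to have failed, the rule favours CR whenever the carried score predates the worsening. Against the observed 12-month score, it favours CR only when the carried score is higher than the score after revascularisation. The formulas are the same for either reference, but the likely sign of s is not.

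**The case against.** The protocol's expectation has a basis. The Background and Discussion both report that revascularisation relieves angina more than medical treatment alone. Using post-procedure scores would credit that relief to CR, and the rule avoids this. If the last available score is the baseline one, the patient counts as unchanged; since patients enter with residual symptoms, that works against CR. All of this stands, so the rule may well be conservative on average. It does not stand as a guarantee.

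The schedule of the SAQ-7 itself is in Table 3, which is not available here. The three-monthly statement in Design is general, and other instruments are collected at fewer visits. How old a carried score could be is therefore unknown, and stale scoring is a possibility rather than an established fact.

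A reader might infer three stronger points that the article does not support:

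- **That conservatism and 80% power contradict each other.** They do not. One concerns bias at the margin and the other power at a design alternative. If "assuming equal means for both groups and a non-inferiority margin of 7 points" refers to the endpoint as analysed, after the rule, 80% stands. The more natural reading is actual 12-month scores, and the power loss follows only on that reading.
- **That defining crossover in one arm is itself a flaw.** Control is angiography with revascularisation where appropriate, so a repeat procedure there is part of the assigned strategy.
- **That the lack of a supplementary analysis or a power table is an error.** These may be in a full protocol or SAP that is not shown. The point rests on what the article states: the label, the rule and the claim.

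**Conclusion.** The point holds in a limited form. The article applies an intention-to-treat label to an analysis that replaces 12-month outcomes after crossover, and it calls the rule conservative without a basis that covers deterioration between assessments. The sample size of 195 (216 with dropout) is correctly calculated, but the 80% holds only if the means are equal after the rule is applied.

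For an assumed net shift of 0.5 to 2 points, type I error is about 4–12% if the rule favours CR, or power is about 74–52% if it disfavours CR and the actual means are equal. These ranges illustrate sensitivity and are not predictions, because the article gives neither a crossover rate nor a score difference. It would go too far to conclude that the rule is biased towards CR overall: the direction is open, and that is the defect.

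**What to change.** 1. Collect an SAQ-7 when revascularisation of a CR patient is decided, before the procedure, and use it as the pre-switch score. This changes a measurement only, not when or whether anyone is revascularised. A fallback to the lowest earlier score should be avoided, since it would build a downward bias into one arm.
2. Stop calling the carried-forward analysis intention-to-treat and name what it estimates. Pre-specify, and report alongside it, an ANCOVA of the observed 12-month SAQ for everyone randomised. Requiring both analyses to succeed is not needed for this point and would cost power.
3. In Statistical analyses, remove the unqualified claim of conservatism. In Sample size calculation, state that 80% power assumes no net effect of crossover, and show power over an assumed range, as in the table above.

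The cost is one short questionnaire per crossover, one extra model and a less favourable power statement. These changes do not restore power; step 5 of the working shows what that would take. Trial status reports 38 of 216 patients enrolled by April 2023, so at that date the extra score could still be collected for most patients.

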#### Cost analyses

For the cost analysis, the primary analysis will be based on the comparison between the two treatment arms. Cost is usually a parameter with a skewed distribution. If this occurs, as well as possible heteroscedasticity, cost analysis will be performed using a generalised linear model with a log ink function relating the conditional mean to independent variables and using a gamma distribution specifying the relationship between the variance and the mean.

For the utility analysis, health utility scores over time will be used. Quality adjusted life years will be calculated by taking the product sum of the health utility scores and the periods in-between successive measurements during the 12 months of follow-up according to the trapezium method. Utilities will be analysed using tobit regression.

The cost-utility analysis integrates costs and utilities to an Incremental Cost-Effectiveness Ratio with bootstrapped confidence intervals surrounding the point estimate of this ratio.

Analysis will be carried out in the statistical software package R.

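### The only model named for utilities is tobit, whose default coefficient is not the mean QALY difference an ICER needs, and the plan does not say which estimate enters the ratio

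*Protocol article*

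**What the plan says.** All references are to the protocol article; no separate SAP is at hand.

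- **Measurement** (Cost analysis): "The questionnaire is held at baseline, 3, 6, 9 and 12 months of follow-up". The scores are converted to utilities with population tariffs.
- **QALY** (Cost analyses): "Quality adjusted life years will be calculated by taking the product sum of the health utility scores and the periods in-between successive measurements", by the trapezium method over 12 months.
- **Model** (Cost analyses): "Utilities will be analysed using tobit regression". No covariates are listed, no censoring limit is given, and nothing says whether the latent coefficient or a mean on the observed scale is reported.
- **Ratio** (Cost analyses): "The cost-utility analysis integrates costs and utilities to an Incremental Cost-Effectiveness Ratio with bootstrapped confidence intervals". The estimator for the utility part is not named.
- **Elsewhere** (Statistical analyses): for secondary endpoints, "Differences between the two groups will assessed using ANCOVA for continuous variables and logistic regression for dichotomous variables". EQ-5D-5L quality of life is listed among those endpoints under Clinical outcomes. Baseline adjustment is spelled out for the primary outcome: "The ANCOVA analysis will be adjusted for baseline SAQ-score values and sex".

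Costs, if skewed, go into a gamma model with a log link, which targets the conditional mean.

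**The concern.** Tobit is designed for measurements cut off by the instrument, where the true value lies beyond the limit and is of interest. Nothing lies beyond full health on the utility scale. When patients sit at 1, the tobit coefficient describes a shift in a hypothetical variable and exceeds the shift in actual mean utility.

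The ICER divides a mean cost difference by a mean QALY difference. The plan names a mean-scale model for costs and a latent-scale model for utilities, then combines the two without saying how the second is brought back to the mean scale. Putting the tobit coefficient in the denominator would overstate the QALY difference in whichever direction it falls, and so shrink the ICER towards zero. Cost-effectiveness is part of the trial's second aim, and the Discussion ties cost to the case for national implementation.

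A second, smaller matter is precision. Baseline utility enters the trapezium QALY directly and is correlated with every follow-up score, yet no adjustment for it is attached to the utility model.

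**Working it through.** **Plan's own figure.** There is none for utilities or QALYs. The stated sample size (195, inflated to 216) uses only SAQ inputs. SD, ceiling share and correlation below are therefore assumptions, shown as ranges.

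**1. Trapezium weights.** Visits at 0, 3, 6, 9 and 12 months are 0.25 years apart. The end visits get 0.25/2 = 0.125 each and the three inner visits 0.25 each. The sum is 1.

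**2. Single-visit utility, closed form.** For a latent normal with mean μ and SD σ, capped at 1, with a = (1 − μ)/σ:

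observed mean = μΦ(a) − σφ(a) + 1 − Φ(a).

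Take σ = 0.2 and a latent shift of 0.03.
- μ = 0.80, a = 1: 0.6731 − 0.0484 + 0.1587 = 0.7833, with 16% at the ceiling.
- μ = 0.83, a = 0.85: 0.6659 − 0.0556 + 0.1977 = 0.8080.
- Observed difference 0.02467; ratio 0.03/0.02467 = 1.22.

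The same steps give 1.33 with 23% at the ceiling (μ = 0.85) and 1.51 with 31% (μ = 0.90).

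**3. Single visit against annual QALY, simulation.** Settings: 97 per arm, 400 runs, five visits, correlation 0.5, σ = 0.2, latent shift 0.04 at the four follow-up visits.

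| Latent mean | At 1, month 12 | Month 12: observed / tobit | Ratio | QALY equal to 1 | QALY: observed / tobit | Ratio |
|---|---|---|---|---|---|---|
| 0.80 | 18% | 0.0330 / 0.0404 | 1.22 | 2% | 0.0284 / 0.0290 | 1.02 |
| 0.85 | 26% | 0.0303 / 0.0405 | 1.34 | 4% | 0.0262 / 0.0271 | 1.04 |
| 0.90 | 35% | 0.0263 / 0.0402 | 1.53 | 7% | 0.0226 / 0.0245 | 1.09 |

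The annual QALY equals 1 only for a patient who scores 1 at all five visits, so its ceiling is much smaller. Letting the correlation run from 0.5 to 0.7 gives about 1.18-1.52 for one visit and 1.02-1.17 for the QALY.

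**4. Effect on the ratio, if the latent coefficient were the denominator.** The ICER is divided by the factor. Factors of 1.2 to 1.5 leave 1/1.2 = 0.83 to 1/1.5 = 0.67 of its value. Factors of 1.02 to 1.17 leave 0.98 to 0.85.

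**5. Baseline utility.** With σ = 0.2 and 108 per arm, the SE of the chance baseline difference is 0.2 × √(2/108) = 0.0272. With correlation ρ, an imbalance carries into the unadjusted QALY difference with slope 0.125 + 0.875ρ.
- ρ = 0.5: slope 0.5625, so a 1-SE imbalance moves the result by 0.0272 × 0.5625 = 0.0153.
- ρ = 0.7: slope 0.7375, giving 0.0201.

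In the simulation at ρ = 0.5, adjustment lowered the sampling SD of the QALY difference from 0.0197 to 0.0132, from 0.0168 to 0.0122 and from 0.0161 to 0.0121 in the three rows: reductions of 33%, 28% and 25%. Over ρ = 0.5 to 0.7 the reduction is about 28-50%; the lower end is uncertain by a few points from simulation error. The average estimate was essentially the same with and without adjustment (for example 0.0262 and 0.0264).

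**The case against.** The strongest reply is that the path from tobit to the ICER is inferred. The section describes three steps (QALYs, tobit, ratio) and never says that the tobit coefficient is the denominator. Bootstrapping patient-level cost and QALY pairs and taking arm means would fit the text, as would an observed-scale prediction from the tobit model. This stands. A reader might infer that the planned ICER is biased; the document does not establish that.

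A reader might also apply the factor of 1.2 to 1.5 to the QALY difference. That factor belongs to single-visit utilities. It would reach the QALY only if visit-level tobit coefficients were combined through the trapezium weights. For a tobit on the QALY itself the overstatement is small.

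Third, a condensed article commonly leaves a covariate list to the full protocol or SAP, and this trial uses ANCOVA for its other continuous secondary endpoints. That stands too: silence is not a stated unadjusted analysis and is no error in itself. Nor is chance imbalance under 1:1 randomisation a systematic bias. It is sampling variation, already contained in the unadjusted standard error. No utility or QALY effect of interest is stated, so the imbalance cannot be called large against one.

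What the reply does not remove is that the article does name a model, and only one. Its default output is not the quantity the next step needs. That is a fixed choice left unconnected to its use, not merely an omitted detail.

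**Conclusion.** The point holds in a limited form. Tobit is the only named utility model, 1 is a true maximum, and the default coefficient is a latent-scale difference rather than the mean QALY difference. If it were used, the overstatement would be about 1.2 to 1.5 times for single-visit utilities with 16-35% at the ceiling, and about 1.02 to 1.17 times for the annual QALY. These figures rest on an assumed normal latent utility with SD 0.2 and a between-visit correlation of 0.5 to 0.7. The case for baseline utility adjustment is precision and removal of chance imbalance from the realised estimate.

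This is a minor-to-moderate point on the secondary economic analysis. It leaves the SAQ comparison, its margin and the sample size untouched.

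**What to change.** State in the analysis plan that the QALY difference in the ICER is the observed-scale mean difference. Obtain it from a linear regression of each patient's 12-month trapezium QALY on arm and baseline EQ-5D-5L utility. Bootstrap that regression jointly with the cost model, resampling patients so that the correlation between costs and QALYs is kept. Keep tobit as a sensitivity analysis, or report it as marginal means on the observed scale rather than as the latent coefficient.

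The cost is a few sentences of analysis wording. Baseline utility and all follow-up scores are already scheduled, so no new data, visits or patients are needed.
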